## Abstract

**Background/Objectives**: Toileting-related falls may arise from interacting urinary symptoms, impaired mobility and balance, cognitive or psychological factors, environmental hazards, and caregiver limitations that are often managed separately. This study aims to evaluate the implementation, safety, and 6-month clinical outcomes of an integrated multidisciplinary prevention, treatment, and rehabilitation pathway for older adults and people with disabilities at risk of toileting-related falls. **Methods**: This multicenter, prospective, single-arm implementation study will enroll 300 adults aged ≥18 years across 15 centers. Participants will undergo standardized assessment of urinary function, gait and balance, physical function, psychological/cognitive factors, activities of daily living, fall history, and toileting-related environmental risks. Prespecified risk domain criteria will guide individualized urinary, rehabilitation, psychological/cognitive, caregiver, and environmental interventions, with reassessment and adjustment during follow-up. The primary outcome will be the 6-month cumulative incidence of at least one toileting-related fall. The secondary outcomes will include nighttime and total falls, urinary symptoms, nocturia, mobility, and functional independence. The implementation will be evaluated using RE-AIM and intervention fidelity measures. **Expected Results**: The study will characterize pathway reach, adoption, delivery, fidelity, safety, follow-up performance, data completeness, clinical event rates, and within-participant change. **Conclusions**: The findings may support a reproducible multidisciplinary care pathway and inform subsequent comparative evaluations of effectiveness, sustainability, component contributions, and resource use.

## 1. Introduction

Falls are a major public health problem and an important cause of injury, disability, loss of independence, and death in older adults. The burden is particularly high among people with frailty, disability, functional limitation, or dependence on caregivers. International guidance therefore recommends systematic risk identification, multifactorial assessment, tailored intervention, and longitudinal management rather than isolated single-component prevention strategies [1,2].

Toileting-related falls represent a distinct high-risk clinical scenario. They frequently occur during urgent or nighttime movement to and from the toilet, during transfer onto or off the toilet, or when a person mobilizes without sufficient assistance. Hospital studies show that many occur at night and that affected older adults often have overlapping cognitive impairment, urinary incontinence, gait instability, visual impairment, and dependence in daily activities [3,4]. These events are therefore better understood as the downstream result of interacting urinary, functional, cognitive, environmental, and care system vulnerabilities rather than as isolated environmental accidents.

Lower urinary tract symptoms can increase exposure to hazardous toileting situations. Urinary urgency, voiding difficulty, and nocturia are associated with incident or recurrent falls [5,6]. Systematic evidence also links overactive bladder and urgency urinary incontinence with increased risks of falls and fractures [7,8], supporting the need to consider urinary symptoms together with mobility and functional risk.

Fall prevention evidence supports multifactorial and multicomponent approaches when modifiable risks coexist [9,10]. Exercise targeting balance, gait, and muscle strength is a central component of fall prevention, and recent meta-analytic evidence further supports functional exercise for maintaining strength, functional capacity, and independence in older adults [11,12]. Environmental hazard reduction can also benefit high-risk community-dwelling older adults [13]. However, urinary symptom management, rehabilitation, psychological support, caregiver involvement, and environmental modification are often delivered in parallel rather than through a unified pathway, leaving interactions between these risks insufficiently addressed.

The present program is developed to address this gap by using the toileting scenario as a common endpoint of multiple interacting risks. It integrates urinary function, gait and balance, physical function, psychological/cognitive status, activities of daily living, environmental safety, and caregiver support within a closed-loop process of screening, multidimensional assessment, risk stratification, individualized intervention, follow-up, feedback, and dynamic adjustment. A theoretical model of lower urinary tract symptoms and falls similarly highlights urgency-driven movement, gait instability, divided attention, and executive dysfunction during toileting [14]. The study will evaluate its prospective implementation, safety, and clinical outcomes across participating centers. We hypothesize that a standardized risk-based pathway can be implemented consistently across different levels of care, as reflected by the prespecified RE-AIM and fidelity measures, while providing prospective estimates of 6-month toileting-related falls and changes in urinary, mobility, and functional outcomes. Because there is no concurrent control group, the clinical outcomes will be descriptive and hypothesis-generating rather than evidence of causal effectiveness.

## 2. Materials and Methods

### 2.1. Study Design and Setting

This multicenter, prospective, single-arm interventional implementation study will be conducted at 15 Chinese centers representing different levels of healthcare delivery: four tertiary Grade A hospitals, five secondary hospitals, and six primary-level hospitals. Chinese PLA General Hospital is the coordinating center.

The participating centers must have access to the target population; a designated local study team, the capacity to complete standardized multidimensional assessment and longitudinal follow-up; the ability to deliver or coordinate the core intervention domains; and the capacity to comply with common training, case report forms, fall surveillance, data quality, safety reporting, and ethical requirements. These minimum operational requirements are intended to preserve a common implementation standard across settings.

Including different levels of care is intentional and will allow for evaluation under real-world variations in case mix, staffing, rehabilitation capacity, equipment, and service organization. All centers will use the same eligibility criteria, assessment and intervention-assignment framework, outcome definitions, monthly fall surveillance schedule, documentation, training, and safety procedures. Specific intervention modalities may vary with participant-level clinical indications and local resources, but the underlying assessment and decision framework will remain standardized.

All participants will enter the same integrated pathway. There is no concurrent control arm, treatment allocation, or masking because the interventions are assigned based on a prespecified risk assessment and clinical indications.

The pathway comprises screening and consent, standardized baseline assessment; risk stratification; individualized multicomponent care; monitoring; reassessment; and adjustment according to response, adherence, safety, and changing risk. The follow-up will last 6 months (Figure 1; Table 1).

Figure 1 summarizes the screening, baseline assessment, risk stratification, individualized multicomponent intervention, monitoring and adjustment, 6-month outcome assessment, and integrated clinical and RE-AIM evaluation.

The protocol follows relevant prospective study-reporting principles and SPIRIT guidance [15,16].

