The physical assessment will include strength, joint mobility, transfers, sit-to-stand performance, gait, balance, mobility aids, and functional dependence. POMA will be performed at baseline and Month 6 in participants who can safely stand and ambulate, using habitual aids if needed; non-ambulatory or medically unsafe participants will not be tested [21]. MBI will assess activities-of-daily-living independence at baseline and Month 6 using participant, caregiver, and clinical information as appropriate [22].

The psychological/cognitive assessment will include fear of falling, anxiety, depressive symptoms, cognition, cooperation, and caregiver support. PHQ-9 and GAD-7 will be used at baseline when reliable self-reporting is possible [23,24]. FES-I will be used in participants able to self-report and who undertake standing, transfer, or ambulatory activities relevant to toileting [25]. Protocol-defined non-administration will be documented.

The environmental and care assessment will address nighttime lighting, bed-to-toilet route, floor hazards, thresholds, handrails, toilet height, bedside toileting devices, and caregiver response. The assessment–intervention–outcome matrix is shown in Table 3.

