### 2.10. Training, Intervention Standardization, Fidelity Assessment, and Quality Assurance

Before implementation, the relevant staff will receive standardized training on eligibility assessment, multidimensional evaluation, risk stratification, intervention assignment and principles, device use when applicable, data collection, confidentiality, and safety reporting. Common manuals, CRFs, and intervention assignment checklists will be used across centers, and training completion will be documented for the personnel involved in assessment or intervention delivery.

Participant-level fidelity will assess completion of protocol-required and clinically applicable baseline assessments; documentation of identified risks and assigned domains; concordance between risks and assigned interventions; initiation of planned interventions or a documented reason for non-delivery; major modifications and their reasons; and completion of required follow-up and safety documentation. Concordance will quantify both whether assigned domains are supported by documented baseline risks and whether clinically relevant risks receive an intervention or a documented reason for non-delivery.

Center-level implementation consistency will be evaluated using assessment completion, risk–intervention concordance, intervention delivery and documentation, adherence to monthly fall surveillance, follow-up completion, data completeness, and protocol deviations. Indicators will be summarized separately for each center and, where informative, by center type.

The coordinating center will review these indicators periodically. Recurrent deficiencies will trigger clarification, targeted retraining, and corrective feedback while preserving the common core protocol and documentation standards.

Fidelity deviations will include unjustified omission of required assessment, intervention assignment without documented indication, omission of indicated intervention without explanation, or failure to document a major care plan modification.

Quality control will cover process fidelity, data quality, and safety through standardized CRFs, range/logic and missing data checks, staff competency and equipment checks, adverse event documentation, and escalation procedures.

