### 2.15. Statistical Analysis

The analyses will follow a prespecified statistical analysis plan using R software (version 4.4.3; R Foundation for Statistical Computing, Vienna, Austria). The continuous variables will be summarized as mean (SD) or median (IQR) according to the distribution, and the categorical variables as n (%). The distributional assumptions for the continuous variables and change scores will be assessed by histogram and quantile–quantile plots, supplemented by a Shapiro–Wilk test. Effect estimates will be accompanied by 95% confidence intervals where appropriate. The clinical analyses will be exploratory because the single-arm design has no concurrent comparison group.

The primary outcome will be reported as a proportion with a 95% confidence interval. Participants with a documented toileting-related fall before loss to follow-up will remain event positive; those without a documented event who discontinue before completing the 6-month ascertainment will have an incomplete primary outcome status rather than be classified as event free.

Nighttime toileting-related and total recurrent falls will be summarized as counts and person-time rates. A negative binomial regression with the log follow-up time as an offset will be the primary event rate model. Adjusted exploratory models will include the center as a random intercept when stable; if sparse events or non-convergence prevent estimation, the observed counts and person-time rates with confidence intervals will be reported descriptively.

The continuous secondary outcomes with applicable paired baseline/Month 6 measurements will be summarized as the within-participant change with 95% confidence intervals and analyzed using paired t tests or Wilcoxon signed-rank tests according to the change-score distribution. Additional repeated observations will be analyzed with linear or generalized mixed-effects models accounting for the within-participant correlation.

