The RE-AIM and intervention fidelity outcomes will be summarized according to their prespecified operational definitions using frequencies, proportions, and 95% confidence intervals where appropriate, overall and by center. The risk–intervention concordance, fidelity deviations, assessment completion, intervention delivery, data completeness, and follow-up completion will be reported transparently. Intervention exposure will be described by the intervention domains and components received, initiation and delivery, adherence where applicable, and major modifications during follow-up, both overall and, where informative, by center and relevant participant subgroups. Because intervention assignment and intensity will be individualized according to clinical indications, the exposure analyses will remain descriptive and will not be used to infer causal treatment effects.

Enrollment, follow-up completion, and evaluability will be reported separately with reasons for loss and missing data patterns. For the primary outcome, extreme-case sensitivity bounds will alternatively classify participants with incomplete 6-month status and no prior documented toileting-related fall as event positive or event negative. The continuous secondary outcomes will use available paired measurements with missingness reported.

No multiplicity adjustment is planned for exploratory clinical or subgroup analyses. Tests will be two-sided, with an emphasis on effect estimates and 95% confidence intervals.

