The study also has important limitations. The absence of a concurrent control group prevents causal attribution of changes in fall outcomes or functional measures to the integrated program. Observed within-participant changes may reflect the intervention, natural recovery or deterioration, regression to the mean, concurrent clinical care, or other time-related factors; clinical outcomes will therefore remain exploratory and hypothesis-generating. Participants will intentionally be heterogeneous in age, disability or functional impairment, comorbidity, urinary symptoms, mobility, care setting, caregiver support, and intervention exposure. The prespecified subgroup analyses will characterize this heterogeneity descriptively rather than confirm differential effects. In addition, participants may receive different combinations and intensities of urinary, rehabilitation, psychological/cognitive, caregiver, and environmental interventions; consequently, any observed clinical change cannot be reliably attributed to a single component of the pathway. Fall ascertainment may remain vulnerable to incomplete reporting despite the monthly structured surveillance, and not all symptom or functional instruments will be applicable to every participant. Variations in staffing, equipment, rehabilitation capacity, case mix, and local service organization may also contribute to inter-center differences in delivery. The common core protocol, standardized training and documentation, uniform surveillance, prespecified assignment criteria, and center-level fidelity monitoring are intended to limit this variability, but the center and center-type findings will remain descriptive rather than confirmatory.

If the integrated pathway demonstrates acceptable implementation, fidelity, safety, and follow-up performance, subsequent research should evaluate its effectiveness using comparative designs, such as pragmatic controlled or cluster-randomized studies and should examine the cost, resource use, sustainability, and the contribution of individual intervention components. The anticipated findings will be relevant to care delivered jointly by urology, rehabilitation medicine, nursing, psychology, geriatrics or primary care and community or long-term care services. Coordinated multidisciplinary implementation is therefore a central feature of the program rather than an ancillary component.

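### Section 2.1 rules out all masking for a reason that concerns only intervention assignment, and nothing separates the Month 6 POMA and MBI rater from the staff who deliver care

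*Protocol article*

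**What the plan says.** Section 2.1 excludes masking together with a control arm and allocation, and gives one reason for all three: "There is no concurrent control arm, treatment allocation, or masking because the interventions are assigned based on a prespecified risk assessment and clinical indications".

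Section 2.7 sets the two staff-rated functional measures. For mobility, "POMA will be performed at baseline and Month 6 in participants who can safely stand and ambulate, using habitual aids if needed". For daily living, "MBI will assess activities-of-daily-living independence at baseline and Month 6 using participant, caregiver, and clinical information as appropriate". Changes in both are secondary outcomes (section 2.12.2, Table 5).

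On who does the assessing, section 2.1 requires each center to have "a designated local study team, the capacity to complete standardized multidimensional assessment and longitudinal follow-up", and also to be able to deliver or coordinate the interventions. Section 2.10 says "training completion will be documented for the personnel involved in assessment or intervention delivery". No independent or central rater is mentioned.

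Section 2.15 has the paired changes "analyzed using paired t tests or Wilcoxon signed-rank tests according to the change-score distribution", and adds: "Tests will be two-sided, with an emphasis on effect estimates and 95% confidence intervals".

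Section 4 gives the explanations for change that the authors recognize: "Observed within-participant changes may reflect the intervention, natural recovery or deterioration, regression to the mean, concurrent clinical care, or other time-related factors". Sections 1, 2.2, 2.15 and 4 say that the clinical outcomes are exploratory and not evidence of causal effect.

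**The concern.** How interventions are assigned explains why participants and providers know what is being given. It is no reason for the person scoring function at Month 6 to be someone who delivered the rehabilitation, or to have the baseline score in view. The article excludes masking as a whole, so the choice is stated, but the reason covers only part of it.

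POMA is scored by an observer, and MBI draws on several sources with room for judgment. With a control group, a rater tendency common to both groups would largely cancel. Here there is none, so the tendency becomes part of the reported mean change, and a larger sample only narrows the interval around the shifted value. If the raters' roles differ between hospital levels, the shift may differ as well.

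The non-causal label does not cover this. It warns that a real change may not be due to the pathway, whereas rater expectation means that the recorded change may itself be partly unreal.

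**Working it through.** **Passages side by side**

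1. Reason for no masking (2.1): interventions follow risk and indication. This concerns treatment and says nothing about scoring.
2. Who rates POMA and MBI: not stated. Section 2.1 places assessment capacity with the local team and delivery with the same center. Section 2.10 treats assessment and delivery personnel together and states no separation of roles. That center staff rate is therefore an inference.
3. Safeguards (2.10): training, manuals, common forms and competency checks. These standardize procedure but do not address expectation or sight of an earlier score.
4. Limitations (4): the listed explanations are clinical or time-related. Incomplete fall reporting is acknowledged separately, so measurement error is within the section's scope, but rater expectation is not named.

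**The plan's own figures**

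Section 2.14 gives half-widths for a proportion near 50%, from 1.96 × √(0.25/n):

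| n | Computed (points) | Stated (points) |
|---|---|---|
| 300 | 5.66 | 5.7 |
| 270 | 5.96 | 6.0 |
| 255 | 6.14 | 6.1 |
| 240 | 6.33 | 6.3 |

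They reproduce and do not depend on this point. The plan gives no figure for POMA or MBI change.

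**Illustration for POMA**

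All inputs here are assumptions:

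- SD of change: 4 points (range 3 to 5).
- Number of pairs: 200 (range 150 to 240). Section 2.14 expects 240 evaluable at 20% loss, and POMA is not done in participants who cannot safely stand and walk.
- Average rater shift b: 0.5 or 1 point.
- True change: zero.

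SE = SD/√n = 4/√200 = 0.283. Half-width = 1.96 × 0.283 = 0.55 point.

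P(interval excludes 0) = Φ(b/SE − 1.96) + Φ(−b/SE − 1.96)

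- b = 0.5: b/SE = 1.77, so Φ(−0.19) plus a negligible term = 0.42.
- b = 1: b/SE = 3.54, so Φ(1.58) plus a negligible term = 0.94.
- With no shift the value is 0.05.

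Range over the assumed SDs and numbers of pairs:

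| Shift | Least sensitive (SD 5, n = 150) | Most sensitive (SD 3, n = 240) |
|---|---|---|
| 0.5 point | 23% | 73% |
| 1 point | 69% | over 99% |

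**Same check without choosing an SD**

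This uses a two-sided paired t test (noncentral t), with the shift in units of the SD of change:

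| Shift | n = 150 | n = 240 |
|---|---|---|
| 0.1 SD | 0.23 | 0.34 |
| 0.2 SD | 0.68 | 0.87 |
| 0.3 SD | 0.955 | 0.996 |

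At n = 240, an observed mean change of about 0.13 SD is enough for p < 0.05. The second table applies equally to MBI if its number of pairs is in this range.

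**The case against.** **Single-arm wording.** With one pathway there is no arm to conceal from an assessor, so the section 2.1 sentence can be read as ordinary. That is right about masking to arm. It does not explain why the rater should be part of the care team or see the earlier score.

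**Condensed article.** Who rates, and what the Month 6 form displays, may be settled in a manual or CRF that is not shown. This stands in part. A reader might infer that the article says treating staff rate POMA and MBI, or that baseline scores are on view. It says neither. What remains is a blanket exclusion whose stated reason does not reach outcome rating.

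**Direction.** A reader might infer that the bias is always favorable. The document does not support that: a rater who sees the earlier score may anchor to it and understate change.

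**Assumed size.** The 42% and 94% follow from chosen shifts and do not show that such shifts occur. The plan also puts its emphasis on estimates and intervals rather than tests. Both points are correct. The figures show only how sensitive an uncontrolled interval is to a small shift.

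**Weak remedies.** Hiding the baseline score leaves the rater aware of the visit and the pathway. A comparison by rater role is confounded with center, hospital level and case mix. Both limits are accepted. The measures reduce or expose the problem but do not remove it, and the comparison cannot estimate the bias.

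**Limited consequence.** The outcomes are secondary and labeled exploratory. That lowers the importance, but the label speaks to cause and not to measurement.

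**Conclusion.** The point holds as a modest one that should be corrected. Section 2.1 excludes all masking for a reason that applies to treatment only. The article states no separation between the Month 6 POMA and MBI raters and the providers, the paired single-arm analysis passes any systematic rater shift into the mean change undiminished, and section 4 does not name it.

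The bias is possible, not shown, and its size cannot be derived from the document. Under the assumed SD of 4 points and 200 pairs, a 0.5-point shift with no true change would make the interval exclude zero 42% of the time (23% to 73% over the assumed ranges). The conclusion also rests on the inference that center staff do the rating.

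A reader might go further and take this as undermining the trial's main result. It does not. The primary fall outcome and the precision figures in section 2.14 do not use POMA or MBI ratings.

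**What to change.** 1. **Section 2.1:** limit the stated reason for no masking to participants and providers.
2. **Sections 2.7 and 2.11:** state that, where existing center staffing allows, Month 6 POMA and MBI are rated by a trained team member who does not deliver that participant's rehabilitation, and that the baseline score is not displayed at that rating.
3. **CRF:** record for each rating whether the rater delivered care to the participant. Show POMA and MBI changes by this flag, descriptively only, with a note that the flag is confounded with center, hospital level and case mix.
4. **Section 4:** add rater expectation to the explanations for within-participant change.

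The cost is a form or data-capture display setting, one CRF field, one descriptive table and a few words of text, with no added staff. The downside is some scheduling effort, and small centers may be unable to separate the roles, which the flag would show. Section 2.18 reports that recruitment had not begun on 1 August 2026, so at that date the forms could still be changed before the first baseline rating.
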